## Objectives of the study

We will conduct the first RCT to compare the efficacy and cost-effectiveness of three telephone-delivered brief interventions for alcohol misuse in young people. Participants will receive: (i) 1 session of assessment feedback and information (AF/I); (ii) 2 sessions of AF/I plus MI, or (iii) 2 sessions of a new personality-targeted intervention (PI) incorporating AF/I and MI. This study will identify the most efficacious and cost-effective telephone-delivered BI for reducing alcohol misuse and related problems in young people presenting to EDs/crisis support services. Telephone-delivered BIs provide an innovative, youth friendly and accessible way of delivering treatment to the 99% of young people who own a mobile phone.

*It is hypothesised that e*fficacy will be greatest for PI, followed by MI, and then AF/I at 1, 3, 6 and 12 months in terms of:

(i) the primary outcome variables of alcohol use and related problems, and

(ii) secondary outcome variables of mental health symptoms, functioning, severity of problematic alcohol use, alcohol injuries, alcohol-related knowledge, coping self-efficacy to resist using alcohol, and cost effectiveness

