A two-pronged economic analysis will be conducted. An analysis alongside the trial will display the costs against their benefits in both natural units, such as alcohol-related injuries/illnesses avoided, and QALYs. Costs saved will also be estimated by quantifying visits to GPs and other health service use avoided under the intervention. MI and PI will be assessed against the AF/I arm as comparator. Uncertainty in the assessment will be estimated using non-parametric bootstrapping. In the second modelled CEA, the estimated change in alcohol consumption from the trial will be extrapolated to the general Australian population of 16-25 year olds. The interventions will be evaluated using a model developed for the Assessing Cost-Effectiveness of Prevention (ACE-Prevention) project [74], which determines DALYs averted by an intervention from changes in risk of 20 alcohol-related diseases and injuries. By using this model, we can compare cost-effectiveness of the PI and MI intervention with other alcohol interventions and up to 150 other preventive interventions (e.g., for illicit drugs, obesity, etc.) that have already been evaluated for the Australian population. Data on alcohol-related diseases and injuries from the Australian Burden of Disease 2003 study will be updated to 2015. Links between alcohol consumption and these diseases and injuries are based on the Comparative Risk Assessment study. The model is a multi-cohort, multi-disease model that follows up the target population until death or age 100. Uncertainty will be assessed using a combination of non-parametric bootstrapping for the effect size (alcohol consumption) and Monte Carlo simulation for all other variables (with sampling uncertainty).

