## Discussion

Here we report the study protocol of an RCT comparing the efficacy and cost-effectiveness of three telephone-delivered BIs for young people with alcohol-related injuries and illnesses. The primary aim of the study is to identify the most efficacious and cost-effective telephone-delivered BI for reducing alcohol misuse and related problems in young people presenting to crisis support services/EDs.

There is strong evidence for the short-term efficacy of MI for reducing alcohol use in young people compared to no treatment. However, it is unclear if MI is the most efficacious and cost effective type of BI available as trials comparing MI with AF/I have given inconsistent results. Considerable debate remains about the most effective duration, content, context and mode of delivery of BIs for alcohol misuse, and there is significant scope to increase their impact. This study uses an additive design to address these research questions comparing (i) 1 session of AF/I which gives feedback and information, with (ii) 2 sessions of MI which includes AF/I, delivered in an MI style, plus other MI elements, to build readiness to change, negotiate change goals and develop a plan for change and (iii) 2 sessions of PI which delivers AF/I and MI incorporating personality-targeted cognitive behavioral coping skills training to determine if this increases MI’s impact. This will be the first study to examine the effectiveness of PI in young alcohol users outside of a group-based school prevention program and compare its efficacy to other BIs.

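### The economic analysis names AF/I as comparator for both MI and PI and states no PI versus MI increment, which the aim of finding the most cost-effective of the three needs

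*Protocol article*

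**What the plan says.** The aim is a choice among three options. Under Objectives of the study, the trial is to "compare the efficacy and cost-effectiveness of three telephone-delivered brief interventions for alcohol misuse in young people". The Discussion puts it more strongly: "The primary aim of the study is to identify the most efficacious and cost-effective telephone-delivered BI for reducing alcohol misuse and related problems". The hypothesis in the Objectives orders the arms PI, then MI, then AF/I, and lists cost-effectiveness among the secondary outcomes to which that order applies. The Discussion describes the design as additive, with PI included to see whether its coping-skills component adds to what MI achieves.

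The economic part of the Statistical analysis section describes two analyses.

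- **Within the trial:** "An analysis alongside the trial will display the costs against their benefits in both natural units, such as alcohol-related injuries/illnesses avoided, and QALYs". The comparator sentence is "MI and PI will be assessed against the AF/I arm as comparator". On precision it says "Uncertainty in the assessment will be estimated using non-parametric bootstrapping".
- **Modelled:** the change in consumption is carried into a population model in DALYs, and MI and PI are set beside alcohol and prevention programmes already evaluated for Australia.

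Neither analysis names PI versus MI as a comparison.

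**The concern.** To choose among mutually exclusive options, each option has to be compared with the next best one that is not dominated. Equivalently, all options can be ranked together on net benefit. A ratio against a common control answers a narrower question: is this arm better value than AF/I? If MI and PI both pass that test, the two ratios do not by themselves say which to adopt.

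Two things are at stake. A reader may conclude that PI is the arm to fund because it passes against AF/I, when its extra cost over MI buys too little. In addition, two intervals, each against AF/I, do not show how certain the choice between PI and MI is, and that contrast is what the additive design was built to examine.

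**Working it through.** The article gives no costs, QALYs or threshold, so there is no stated figure to reproduce. The costs, QALYs and thresholds below are assumptions chosen to show the mechanism. They do not predict the trial's results.

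**1. Assumed example.** Costs: AF/I $100, MI $200, PI $320. QALYs: 0.700, 0.705, 0.709. The ratio is the cost difference divided by the QALY difference.

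- MI v AF/I: 100 / 0.005 = $20,000 per QALY
- PI v AF/I: 220 / 0.009 = $24,444 per QALY
- PI v MI: 120 / 0.004 = $30,000 per QALY

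Between $24,444 and $30,000, both arms pass against AF/I but PI fails against MI.

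**2. Net benefit in the same example.** Net benefit against AF/I is threshold × QALY gain − extra cost.

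- At $28,000: MI 28,000 × 0.005 − 100 = $40; PI 28,000 × 0.009 − 220 = $32. MI is best, although PI passes against AF/I.
- At $32,000: MI 32,000 × 0.005 − 100 = $60; PI 32,000 × 0.009 − 220 = $68. PI is best, although MI has the lower ratio against AF/I.

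So neither simple reading of the two ratios is safe: not adopting PI because it passes, and not adopting the arm with the lower ratio.

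**3. Range.** Vary PI's extra cost over MI and hold the rest of the example fixed.

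- Extra cost $0: PI v AF/I is 100 / 0.009 = $11,111 and PI dominates MI. The AF/I ratios order the arms correctly.
- Extra cost $80: PI v AF/I is 180 / 0.009 = $20,000 and PI v MI is 80 / 0.004 = $20,000. This is the break-even.
- Extra cost $120: the misleading band is $24,444 to $30,000, as in step 1.

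A second assumed set has a wider gap: MI +$100 and +0.006 QALY, PI +$250 and +0.008 QALY, both against AF/I. The ratios are 100 / 0.006 = $16,667, 250 / 0.008 = $31,250 and, for PI v MI, 150 / 0.002 = $75,000. The band is then $31,250 to $75,000. The size therefore runs from nothing to large, depending on inputs that the article does not give.

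**4. Can the arms still be ranked?** Yes. (PI − AF/I) − (MI − AF/I) = PI − MI, so PI versus MI follows by subtraction. Net benefit against AF/I subtracts the same constant from every arm and so cannot change the order. In the step 1 example it picked the same arm as each arm's own net benefit at all seven thresholds tried, from $15,000 to $50,000. It also did so in all 2,000 replicates of a simulated bootstrap with 130 per arm (390 / 3) at $28,000, as the algebra requires.

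**5. Uncertainty.** The two AF/I contrasts share the AF/I arm. Let v be the variance of an arm's mean net benefit, assumed equal across independent arms. The variance of PI − MI is v + v = 2v. Adding the variances of the two contrasts as if they were independent gives 2v + 2v = 4v, which overstates the standard error by √(4/2) = 1.41. The correct figure needs the arms resampled together, or PI and MI contrasted directly. The article does not say which form its bootstrap takes.

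**The case against.** A reader might infer that the plan compares with AF/I and nothing else, and so cannot identify the most cost-effective arm. The document does not support that. The comparator sentence excludes no further comparison, and step 4 shows that the planned data are enough to rank all three. The modelled analysis also puts MI and PI on one DALY scale.

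A reader might also infer that the stated rule leads to the wrong recommendation. The article contains no threshold and no adoption rule, so the error arises only if someone reads the ratios in isolation. In the second assumed set, net benefit against AF/I at an assumed $50,000 threshold already favours MI: 0.006 × 50,000 − 100 = $200, against 0.008 × 50,000 − 250 = $150 for PI.

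The assumed cost gaps can be challenged too. The article describes MI and PI as matched in time: two 30-minute telephone sessions each, the same therapist qualifications and training day, and the same four check-in calls. Delivery costs may be close. That stands as a limit on the likely size, though other health service costs also count and could differ.

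Finally, this is a condensed article, and a fuller economic plan may contain the missing comparison. Methods such as dominance rules are commonly left to such a plan, and their absence alone would be no finding. Here, however, the article itself states a comparator, and that comparator does not match the aim it declares.

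**Conclusion.** The point holds as a mismatch between the stated comparison and the stated aim. The article names AF/I as comparator for both active arms and states no PI versus MI increment, while promising to "identify the most efficacious and cost-effective telephone-delivered BI for reducing alcohol misuse and related problems". Ratios against AF/I read alone can mislead about PI relative to MI, and separate intervals do not give the uncertainty of that contrast.

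The size cannot be derived from the document. The bands above rest wholly on assumed inputs, and the step toward a wrong choice also assumes that the ratios are read in isolation. Randomisation, sample size, data collection and the efficacy analysis are not affected. This is worth correcting because the Discussion places cost-effectiveness within the primary aim, but it is not a defect that must be cured before the trial can proceed.

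**What to change.** Keep the comparisons with AF/I and add, after the comparator sentence:

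*The three arms will also be compared in a full incremental analysis (ordered by cost, dominated and extendedly dominated options removed, each remaining option compared with the next best, including PI versus MI where neither is dominated), with the probability that each arm has the highest net benefit taken from one bootstrap of all three arms.*

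In the modelled DALY analysis, keep the planned comparison with other evaluated interventions and also report the PI versus MI increment.

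The cost is a little more analysis work. No new data are needed, and bootstrapping is already planned. Adding the text before results are known also removes any room to choose the comparator afterwards. If a full economic plan already contains this, a cross-reference in the article would be enough.

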**Methods/design:**

Participants will be 390 young people aged 16 to 25 years presenting to a crisis support service or ED with alcohol-related injuries and illnesses (including severe alcohol intoxication). This single blinded superiority trial randomized young people to (i) 2 sessions of MI; (ii) 2 sessions of a new PI or (iii) a 1 session AF/I only control. Participants are reassessed at 1, 3, 6 and 12 months on the primary outcomes of alcohol use and related problems and secondary outcomes of mental health symptoms, functioning, severity of problematic alcohol use, alcohol injuries, alcohol-related knowledge, coping self-efficacy to resist using alcohol, and cost effectiveness.

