## Background

Harmful or hazardous alcohol use is endemic among young people in the developed world [1-3]. In Australia, 60% of young people over a 12-month period reported drinking at levels placing them at risk of harm, with up to 30% drinking at levels placing them at weekly or greater risk of injury [1]. Hazardous alcohol use is a major preventable cause of injury, disability and death in young people, as well as a range of adverse mental health, social, educational, vocational and legal outcomes [4]. It is estimated to contribute to 27.5% of all deaths and 19.5% of substance-attributable disability-adjusted life years among 15–29-year-olds in the developed world [4]. In 2009, the economic burden of alcohol was estimated to equate to 0.45-5.44% of Gross Domestic Product (GDP) across 12 countries [5]. In Australia alcohol use represents 1.2% of GDP costing the economy $15 billion annually [6].

The rate of alcohol-related emergency department (ED) presentations in young people has increased dramatically in recent decades [7-9]. This presents a unique opportunity to engage traditionally non-treatment seeking youth into brief alcohol treatment. However, EDs are not ideal settings for the delivery of psychological treatments. Medical treatment for the injury or illness must take priority, and patients’ attention may be impaired by intoxication, distress or the administration of analgesics. An opportunistic intervention involving initial engagement in these settings, followed by delivery of a post discharge telephone-based intervention benefits both acute management and longer term treatment engagement. Global mobile devices and connections grew to 7 billion in 2013 [10]. Ninety-nine percent of young Australians own mobile phones, and overwhelmingly prefer electronic sources of health information over traditional ones [11,12]. Mobile phones provide an innovative, youth friendly and accessible way of delivering treatment.

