Brief interventions (BIs) have a well established evidence-base for reducing alcohol use and related harm in adults [13,14], including adults presenting to EDs with alcohol-related injuries [15]. They typically comprise 1-2 sessions (from 10-15 minutes to 2 × 1 hour sessions) of personalised assessment feedback and information (AF/I). Many BIs include motivational interviewing, a person-centred therapeutic approach designed to assist individuals resolve ambivalence about problem drinking, set tangible goals for and strengthen commitment to change [16].

There is strong evidence for the impact of brief motivational interviewing interventions (MI) on young college students’ alcohol use and related problems at 3 [17-19], 6, 12, 24 and 48 months follow up, compared with no treatment [20,21]. One study has reported positive effects for MI on alcohol use and related problems among adolescents presenting to an ED with alcohol-related injuries at 3 and 6 month follow up, compared to standard care brief advice; [22].

While MI produces demonstrable reductions in alcohol use and related harm, there is significant scope to increase their impact. Most studies comparing MI and no treatment control conditions report small to moderate differences in alcohol use outcomes [20,21]. One reason for this is that treatment effects tend to reduce over time, as young people in control groups also begin to address their alcohol misuse [21,23].

It is unclear which form of BI is most effective for treating youth alcohol misuse as many studies report small effect sizes when comparing MI with other types of BIs. For example, while Monti *et al.*[24] reported ED-based MI was more effective for reducing alcohol use at 6 and 12 months follow up than assessment feedback alone, only small differences in effect size (f’s ranging -.24 to -.33) were found. We recently found two sessions of MI had more impact on alcohol use than an AF/I control at 1 (f = -.62) and 3 months (f = -.51) but not 6 month (f = -.47) follow up, in young people accessing a youth primary care service [25]. However, two further studies comparing MI with AF/I in college students at 6 and 12 month follow up, did not find superiority for MI [26,27].

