### Eligibility criteria

Inclusion criteria are: aged 16-25 years, and either consumed ≥ 6 standard drinks on one occasion in the previous 2 weeks or scored ≥ 8 on the 10-item *Alcohol Use Disorders Identification Test* (AUDIT) [53]. Users of illicit drugs including cannabis are eligible, as long as alcohol is the most frequently used drug (other than tobacco). Exclusion criteria are: (i) ED serious medical problem or traumatic injury; (ii) not fluent in spoken or written English; (iii) unmodified hearing impairment; (iv) estimated IQ < 70 measured by the National Adult Reading Test; (v) current high suicide risk (current suicidal ideation/intent and plan); (vi) current or past history of psychosis; (vii) history of traumatic brain injury or organic brain disease (viii) currently in acute alcohol or drug withdrawal, and (ix) received psychological or pharmacological treatment for a drug or alcohol problem in the previous month.

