Engaging young alcohol users with alcohol-related injuries and illnesses who present to crisis support services and EDs into alcohol treatment is challenging, as they are unlikely to view their alcohol use as problematic or responsible for their injury or illness. Initial engagement in these settings, followed by rapid and assertive follow up and the provision of telephone-delivered BIs targeting their recent alcohol related injury or illness, provides a more youth friendly way of engaging young people into treatment than traditional services. Preliminary piloting of this process has produced positive results with 50-70% of young people referred to the study engaging in a BI depending on the referral source. The following strategies are also used to maximise participation and ensure dropout is below 30%: (i) obtaining multiple ways to contact participants at baseline; (ii) the development of tracking databases; (iii) adopting flexible appointment hours, giving pre-appointment reminders and rapidly following up missed appointments; (iv) a rising reimbursement schedule for the time associated with completing the baseline and follow up assessments, and (v) the assessment of only primary outcome measures when a young person wishes to discontinue treatment or is unwilling to undertake the full follow-up protocol.

The large numbers of young people presenting to crisis support services and hospital EDs with alcohol related injuries and medical conditions present a unique opportunity for engagement in BIs targeting their alcohol use. This may also reduce the risk of future alcohol-related injuries, illnesses, disability and mortality in young people, as well as a range of adverse mental health, social, educational, vocational and legal outcomes. The brief alcohol related interventions evaluated in this study can be easily transferred to existing health professionals across ED and other crisis services as well as primary care, mental health and alcohol and other drug treatment settings. Results of this project are expected to exert a significant influence on clinical policy and practice aimed at increasing access to evidence-based and cost-effective care for young alcohol users aimed at reducing the individual, community and economic costs of youth alcohol misuse.

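### The modelled cost-effectiveness analysis carries an effect measured in hazardous drinkers at an acute presentation over to all Australians aged 16-25, so total DALYs averted could be overstated

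*Protocol article*

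**What the plan says.** The Statistical analysis section plans two economic analyses: one alongside the trial, and a second, modelled one. For the second, "the estimated change in alcohol consumption from the trial will be extrapolated to the general Australian population of 16-25 year olds". An existing prevention model then turns changes in the risk of 20 alcohol-related diseases and injuries into DALYs averted. The results are to be compared with up to 150 other preventive interventions. The model follows a target population until death or age 100, and that population is not defined further. Uncertainty is handled by bootstrapping the effect size and by Monte Carlo simulation of the other sampled inputs.

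The trial population is narrower. The Abstract describes participants as "presenting to a crisis support service or ED with alcohol-related injuries and illnesses". Eligibility criteria adds that they must have "either consumed ≥ 6 standard drinks on one occasion in the previous 2 weeks or scored ≥ 8" on the AUDIT. The Discussion states the primary aim, including the cost-effectiveness aim, for young people who present to these services.

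**The concern.** The modelled analysis names a different population from the one in which the effect is estimated and from the one in the primary aim. The general population aged 16-25 includes abstainers and low-risk drinkers, who have little or no drinking to reduce. It also includes people with no recent alcohol-related injury or illness. The Discussion treats that event as the opportunity for engagement, and the description of PI builds part of Session 1 around it.

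Read literally, the rule credits all these people with the effect seen in selected hazardous drinkers. The uncertainty analysis would not reveal the problem, because resampling trial data and drawing model inputs address sampling error and not transfer to a different population. At stake is the projected national health gain, which the article intends for policy use.

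**Working it through.** The article gives no DALY count, coverage figure or modelled population size, so there is no stated result to reproduce. The check is a bound.

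**Inputs**
- Share of young people resembling the trial, *p*. Background gives a broad proxy, "60% of young people over a 12-month period reported drinking at levels placing them at risk of harm" (*p* = 0.60), and a narrow one, "up to 30% drinking at levels placing them at weekly or greater risk of injury" (*p* = 0.30 at most). Neither matches the entry criteria exactly.
- Effect in the remainder relative to the trial effect, *r*. The documents do not give it, so it is varied from 0 to 1 as an assumption.

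**Formula.** Assume that DALYs averted are proportional to the total change in consumption. Applying the trial effect *e* to all *N* people credits *N* × *e*. The effect actually available is *N* × *e* × [*p* + (1 − *p*) × *r*]. The overstatement factor is therefore 1 / [*p* + (1 − *p*) × *r*].

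**Results**

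| *p* | *r* = 0 | *r* = 0.25 | *r* = 0.5 | *r* = 1 |
|---|---|---|---|---|
| 0.60 | 1/0.60 = 1.67 | 1/0.70 = 1.43 | 1/0.80 = 1.25 | 1.00 |
| 0.30 | 1/0.30 = 3.33 | 1/0.475 = 2.11 | 1/0.65 = 1.54 | 1.00 |

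The share of 16-25 year olds who actually present to an ED or crisis service is not in the documents. Purely as an illustration, an assumed *p* = 0.10 gives 1/0.10 = 10 at *r* = 0 and 1/0.55 = 1.82 at *r* = 0.5. No conclusion is drawn from that row.

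**Cost per DALY.** Let *c* be the cost per person treated.
- If costs and effect are both applied to everyone, the model reports *c*/*e*. A programme confined to people like the trial's participants would also give *pNc*/*pNe* = *c*/*e*. The total is then inflated but the ratio is not.
- If the same *c*/*e* is read as the result of treating the whole population, it is too low by the factor in the table.
- If costs cover only the share *p* while the effect is credited to everyone, the ratio becomes *pc*/*e* and is too favourable even for a restricted programme.

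Presenters may also have a higher baseline risk, so each unit of reduction could avert more harm in them. That would pull the other way.

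**The case against.** **The application rule is not spelled out.** Extrapolating an effect does not necessarily mean giving the same absolute change to everyone. The undefined target population could be narrower, and a condensed article may leave rescaling and coverage to the model specification. This stands as far as it goes, and it is why the conclusion is conditional. It does not remove the point, because the only population the text names for the extrapolation is the general one.

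**Readings that go too far.** A reader might infer any of the following, and the documents do not support them.
- *A several-fold overstatement as established fact.* The article's own shares reach 3.3 only with the narrow share and no effect at all in the other 70%.
- *Larger factors from multiplying by uptake.* One could multiply the national shares by "50-70% of young people referred to the study engaging in a BI" and take the inverse: 0.60 × 0.50 to 0.70 gives 2.4 to 3.3, and 0.30 × 0.50 to 0.70 gives 4.8 to 6.7. That figure is pilot engagement among people already referred, which is a different denominator from a national survey. The main analyses are by intention to treat, so non-engagement after randomisation is already in the effect and the product may count it twice.
- *A biased ranking against other interventions.* The ranking is on cost-effectiveness. Uptake largely cancels in a ratio, and the effect of the population mismatch depends on how costs are scaled.
- *Use of within-arm change, with regression to the mean.* The text speaks of an effect size, and it names AF/I as comparator, although in describing the analysis alongside the trial. The wording permits the other reading but does not plan it.
- *An effect assumed to last for life.* Background does say that "treatment effects tend to reduce over time". But following cohorts to death or age 100 is a tracking horizon and not a statement that the effect persists. Duration can be left to the model specification.

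**Weight.** Cost-effectiveness is a secondary outcome, and the analysis alongside the trial is unaffected. Both are true, and they limit the point to the modelled analysis.

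**Conclusion.** The point holds in a limited form. The stated extrapolation population is wider than the trial population and wider than the population in the primary aim, and the planned uncertainty analysis does not address the gap. Followed as written and without rescaling, the rule could overstate total DALYs averted by up to about 1.7 times (60% share) or about 3.3 times (30% share), falling towards 1.0 as the effect in the remainder approaches the trial effect.

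These bounds assume that DALYs are proportional to the total change in consumption, that the survey shares are acceptable proxies for people like the trial's participants, and that the effect is applied unscaled. Neither the direction nor the size of any bias in cost per DALY can be fixed from the documents.

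**What to change.** Define the base-case modelled population as 16-25 year olds who meet the trial's entry criteria and present to an ED or crisis service, and state the source for its size. Apply the randomised between-arm difference (MI versus AF/I, PI versus AF/I) to that group, and scale costs to the same people. Report the general population aged 16-25 only as a scenario analysis, with the assumed effect in non-eligible people stated and varied.

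The cost is a change of model inputs, a few sentences of text and an external figure for the number of presenters. Trial conduct and the analysis alongside the trial do not change. The projected national benefit becomes smaller.
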